**Recommendations based on mammographic BD information**

In current clinical practice, no formal recommendation exists regarding follow-up of women with dense breasts in clinical mammography or screening. However, in clinical mammography, the need for supplementary imaging is evaluated on an individual basis by the radiologists, taking clinical information and risk factors into account.

In this study, women with all breast density categories will receive recommendations based on the PRS score (or national guidelines for MPV management if MPV is detected).

## **STEP 4. Implementation of personalized screening and prevention (risk reduction)**

### **Next steps after test results**

#### **Personalized Prevention Measures Based on the AnteBC test**

Based on the PRS, it is possible to divide the patient's relative risk of developing BC into different levels compared to the average in the given age, while accurately assessing the risk of a particular percentile. The women will be recommended annual or biennial mammography examination according to risk level and Variant 1-4 listed in Step 3.

The population-based screening program has a central organization with a standardized regime for an invitation, screen-reading, and registration of screening results. Modification of screening logistics as entry age or screening frequency is not possible within the screening program as such. Thus, for women recommended mammographic screening starting at an earlier age (<50) and/or increased frequency (annual screening), these “extra” examinations will be offered as a clinical mammography examination outside the screening program.

The women will be followed for 10 years.

### **5.3. BLODD SAMPLES/BIOBANK**

The women participating in the pilot for PERSONALIZED RISK-BASED BREAST CANCER SCREENING will also be asked to give a wide consent to general biobank for breast cancer in Vestre Viken (REK number 108572). The biobank includes also women that are assessed for breast cancer and precursors for breast cancer. Women that do not have breast cancers are included as controls. The blood samples will be stored for future research. The women can participate in the study without giving consent to general biobank breast cancer. The women will be asked to consent to registry and biobank through a separate box. The consent for general biobank and registry will be given to the women for information, but the women will only sign the pilot study.

### **5.4. ASSESSMENTS**

#### **Baseline Assessments**

- Age
- Date of mammography
- Result of mammography: normal / needs additional specification / tumour
- MD
- Biopsy
- Confirmed invasive cancer
- Confirmed in situ carcinoma
- PRS level

#### **In case of PRS only:**

- Age
- Personal medical history

- Family cancer history
- Current medications (hormonal agents)
- Mammography: normal / needs additional specification / tumour
- MD
- Short- and long-term psychosocial aspects related to genetic feedback (questionnaires after the return of data and after 6 months)

**In case of monogenic pathogenic variants:**

- Age
- Mutated gene
- Type of mutation
- Personal medical history
- Family cancer history
- Description of cancer risk levels
- Short- and long-term psychosocial aspects related to genetic feedback (questionnaires after the return of data and after 6 months)
- Current medications (hormonal agents)
- Mammography
- MD
- MRT

**Variables Collected**

- Name
- Personal ID
- Date of birth
- Age
- Phone
- E-mail
- Postal address
- Preferred contact channel
- Family history for monogenic pathogenic variants (MPV)
- Family history of cancers
- Polygenic risk score (PRS) test results
- MPV test results
  
- Date of mammography
- Result of mammography: normal / needs additional specification / tumor
- Mammographic BD
- Date of biopsy, if performed
- Results of biopsy: Benign / Confirmed invasive cancer / Confirmed in situ carcinoma
- Occurrence and date of medical counselling

**In the case of MVPs:**

- Date of clinical geneticist consultation
- Date of oncologists' consultation

- Date of mammography
  - Result of mammography: normal / needs additional specification / tumor
  - Mammographic BD
  - Date and results of MRT
  - Date and results of abdominal and gynecological ultrasound
  - Date and results of CA125; HE4, if performed.
- 
- Information about possible hormonal chemoprevention (when started, what drug)
  - Information about possible risk-reducing surgeries (when and what)
  - Information about possible detected malignancies: Date, type, stage, TNM, morphology
  - Short- and long-term psychosocial aspects related to genetic feedback (questionnaires after the return of data and after 6-9 months).

### **5.5. Discontinuation/Withdrawal of Participants from Study**

Each participant has the right to withdraw from the study at any time.  
The reason for withdrawal will be recorded in the eCRF.

### **5.6. Definition of End of Study**

Activities with patients for study data collection are planned to finish after 10 years of follow-up.

## **6. STATISTICAL METHODS**

### **6.1. Description of Statistical Methods**

Data will be mainly analysed by descriptive statistics.

### **6.2. Analysis of Outcome Measures**

**Planned data for outcome analyses:**

- Study group characteristics: age, distribution of age groups, and other clinical characteristics.

Additional outcomes:

- Results of SNPs testing and SNP PRS analyses.
- Individuals' distribution into risk groups.
- Individuals' participation rate from additional counselling; analysis of patients' compliance.
- Exact analysis and description of medical activities after counselling.
- Association of PRS score and breast density

Current Terms of Reference for the Study, and study time frame, do not allow for conducting a randomized long-term study, which could be capable to analyse real changes in incidence and mortality of BC.

### **Cost-effectiveness analyses**

During the final stage (last 6 months) of the pilot study, the cost-effectiveness analysis will be conducted.

The cost-effectiveness analysis will aim to estimate the difference in health outcomes and the difference in costs of implementing the personalized medicine interventions as compared to standard care.

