| Planned Sample Size             | 80                                                                                                                                                                                                                                                                                                           |                                                                                                                                                                                                                                                                                                                                                                                                                                                                                                                                                                                                                                                                                 |
| Planned Study Period            | 01.11.2022 – 01.11.2035                                                                                                                                                                                                                                                                                      |                                                                                                                                                                                                                                                                                                                                                                                                                                                                                                                                                                                                                                                                                 |

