### **Variant 2. If the risk is slightly increased - up to two times (moderate increase in risk depending on age):**

- Implement mammography screening at **two-year intervals** from the age at which the risk of the average 50-year-old woman is reached (depending on the age at which the 10-year risk reaches 2.1 %), i.e. screening is recommended for those under 50 years of age due to an increased risk.

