**Variant 3. If the risk is increased two to three times (moderate increase in risk compared to the same age average):**

- Implement mammography screening at **two-year intervals** from the age at which the risk of the average 50-year-old woman is reached (depending on the age at which the 10-year risk reaches 2.1 %).

and/or

- Implement mammography screening at one-year intervals from the age at which the average 50-year-old woman reaches twice the risk level (depending on the age at which the 10-year risk exceeds twice the corresponding age level or for women under 50 from the risk level of  $2 \times 2.1$  %, which is twice the risk level for women aged 50);

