#### Methodology of the cost-effectiveness study

Whereas the whole pilot study aims to develop models for the personalized medicine interventions, it is not possible to predict which efficacy and effectiveness measures will be best suited to estimate the health outcomes of the program.

The planned personalized medicine interventions are preventive, and the pilot project will last less than 2.5 years, thus the most robust health outcome of mortality cannot be achieved during the study. Therefore, additional health outcomes, e.g. disease-free time to diagnosis and/or hospital care, stage of cancer diagnosed will be used to estimate the effect of preventive measures to increase the disease-free life years, postpone the negative health events, and decrease the need to use health care resources will be collected. This data will be used to model the number of events occurring in specified cohorts of persons at risk – a cohort receiving personalized preventive interventions will be compared to that on standard care.

To estimate the long-term effectiveness and costs of the new interventions, economic modeling will be used. The Markov cohort models of the natural history of BC will be constructed to assess the cost-effectiveness of preventive interventions.

The recently published cost-effectiveness studies modelling BC will be used to construct the natural history of the disease. Annual age-specific probabilities of dying from this disease and the health-related quality of life decrement during the illness will be calculated for the Swedish, Estonian and Portuguese cohorts using published cost-effectiveness studies.

The analysis results will be presented as incremental costs and quality-adjusted life-years (QALYs) gained with each intervention compared to no personalized medicine and as incremental cost-effectiveness ratios (ICERs). Both costs and utilities will be discounted at an annual rate of 5%. The sensitivity analysis will be performed by varying one or more similar parameter(s) at a time while holding other parameters at their base case value.

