#### The data used for cost calculations will include

- Direct costs of the use of health care services (out-patient care, hospital care, and pharmaceuticals), based on the data from healthcare systems.
- Costs for developing and maintaining IT solutions for collecting and using health information for personalized medicine purposes.
- Costs for collection and analysis of additional samples arising from the new clinical approaches of the two preventive interventions.
- Costs for disseminating the results of the pilot project to the scale of the whole population: training of health care staff and additional workload estimates related to full implementation of the personalized medicine approach (e.g. motivational interviewing).

Most of this cost data will be collected in parallel to the implementation of the pilot project.

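### The protocol gives conflicting durations for the period that dates the cost-effectiveness analysis; on the shorter one, the analysis stage opens before a biennial examination counted from entry can fall due

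*Protocol*

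**What the plan says.** **Timing.** Protocol Section 6.2, under Cost-effectiveness analyses: "During the final stage (last 6 months) of the pilot study, the cost-effectiveness analysis will be conducted". The methodology paragraph that follows says "the pilot project will last less than 2.5 years" and uses this to explain why mortality cannot be observed.

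**Other durations.** The synopsis gives the study period as "01.11.2022 – 01.11.2035". Section 5.2, Step 4 says "The women will be followed for 10 years". Section 5.6 says "Activities with patients for study data collection are planned to finish after 10 years of follow-up".

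**Inputs.** Section 4 says the model will draw on the clinical pilot together with epidemiological and cost data. Section 6.2 adds, on costs, "Most of this cost data will be collected in parallel to the implementation of the pilot project".

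**Screening schedule.** Women enter after a clinical mammogram without signs of malignancy (Section 5.1). In Step 3, Variants 2 to 4 recommend two-year intervals "from the age at which the risk of the average 50-year-old woman is reached", that is, once the 10-year risk reaches 2.1%. Variants 3 and 4 add, as an and/or option: "Implement mammography screening at one-year intervals from the age at which the average 50-year-old woman reaches twice the risk level".

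**The concern.** Cost-effectiveness is a secondary aim and part of a key hypothesis (Sections 3.7 and 4). What the pilot can add to a model is observed behaviour and resource use: who attends the earlier mammograms, and what care and cost follow. That information exists only after examinations have fallen due.

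If the analysis is tied to a pilot of under 2.5 years, it comes at about the time the first biennial round would start, and the 10 years of planned follow-up have no cost-effectiveness analysis to inform. If it is tied to the end of the study in 2035, the difficulty disappears. The protocol supports both readings, so someone building the model cannot tell which inputs will be observed and which must be assumed.

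**Working it through.** **1. Durations.** From 01.11.2022 to 01.11.2035 is 13.0 years, against less than 2.5 years (30 months) in Section 6.2. The protocol does not say that the shorter period is a phase within the longer one.

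**2. Analysis window.**
- Short reading: the last 6 months of fewer than 30 start before month 30 − 6 = 24.
- Long reading: the last 6 months start at about year 12.5.

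**3. What can be due on the short reading, without simulation.** Suppose the interval is counted from the entry mammogram. A woman on the biennial schedule who enters at month e is first due at month e + 24 or later, which is never before month 24. By a pilot end before month 30 she can be due only if e < 6 and her risk has reached 2.1% by then. With uniform recruitment over 6, 12 or 18 months, the share enrolled in the first 6 months is 6/6 = 100%, 6/12 = 50% or 6/18 = 33%. Before month 24, only women on the annual schedule can contribute observed attendance at a due examination.

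**4. Size, by simulation (400,000 draws per scenario).**

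From the protocol: age 40–49, 10-year risk of 2.1% at age 50, thresholds of 2.1% and 2 × 2.1% = 4.2%, and 80 women.

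Assumed, because the protocol gives no figure:
- age uniform from 40 to 50;
- population 10-year risk at age 40 of 1.2–1.7%, rising log-linearly to 2.1% at 50;
- log-normal PRS relative risk with SD 0.4–0.6;
- uniform recruitment over 6, 12 or 18 months;
- flagged means relative risk above 1.

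Two due rules were compared:
- (a) first due = the earlier of max(24 months, time to 2.1%) and max(12 months, time to 4.2%), counted from entry;
- (b) first due = time to 2.1%, with no interval counted from the entry mammogram.

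| Rule | Recruitment | Flagged women due by month 24 | By month 30 |
|---|---|---|---|
| (a) | 6 months | 3–15% | 67–90% |
| (a) | 12 months | 3–15% | 35–53% |
| (a) | 18 months | 2–10% | 24–40% |
| (b) | 6 months | 63–89% | 67–90% |
| (b) | 12 months | 61–88% | 65–89% |
| (b) | 18 months | 59–87% | 63–88% |

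Under these assumptions 38–42% of women are flagged, or 0.38 × 80 = 30 to 0.42 × 80 = 34 women. Of these, 48–83% are already at 2.1% on entry, so 17–52% start later. Under rule (a), month 24 then means between 0.02 × 33.6 = 0.7 and 0.15 × 30.4 = 4.6 women, all on the annual schedule.

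The table counts examinations that fall due at age 50 or later. Leaving those out lowers the rule (a) figure for 12-month recruitment at month 30 to about 24–42%.

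**5. Long reading.** With a cut at year 12.5 and recruitment of up to 2.5 years (assumed), essentially 100% of flagged women have had an examination fall due.

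**The case against.** The strongest reply is that the whole study is titled a pilot and runs to 2035, so the analysis may fall in its last six months, when nearly every flagged woman has been due. This is a possible reading, and on it the timing problem is gone. It is not the natural one: Section 6.2 invokes the short duration to explain what the study cannot observe. It also leaves the contradiction standing.

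A second reply is that long-term effects and costs are to be modelled in Markov cohorts, and that the protocol openly concedes its limited time frame. That limits the harm for health outcomes, but it does not supply observed uptake or resource use.

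A reader might go further and infer any of the following, none of which the protocol supports:
- **Uptake and cost inputs are biased towards zero.** No section says uptake will be set from pilot attendance. Epidemiological and healthcare cost data are also inputs, and the bias would require counting women not yet due as non-attenders, which is not proposed.
- **Compliance and feasibility are also assessed at this cut.** Section 6.2 dates only the cost-effectiveness analysis.
- **Women not yet due cannot be told apart from non-attenders.** Section 5.4 collects date of birth, mammography dates and PRS results, and the test report gives individual 10-year risk (Section 5.2). Once a due-date convention is fixed, due status can be derived.
- **Most flagged women will have had nothing due by the analysis.** This holds at month 24 under rule (a). It fails under rule (b), and also under rule (a) at month 30 with 6-month recruitment.

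**Conclusion.** The contradiction is firm and needs no assumptions: under 2.5 years in Section 6.2 against 13 years in the synopsis, with 10 years of follow-up in Sections 5.2 and 5.6. The data cut for the cost-effectiveness analysis is therefore undefined.

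The consequence is conditional. On the short reading, with intervals counted from the entry mammogram, no biennial examination is due when the analysis stage opens, and the planned follow-up informs no cost-effectiveness analysis. The size of the gap by the end of the pilot depends on recruitment length and on the due rule, neither of which the protocol fixes, so no single percentage should be quoted. The point is worth correcting because the protocol already plans to collect the data that would close the gap.

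**What to change.** 1. Reconcile the study period in the synopsis, the follow-up in Sections 5.2 and 5.6, and the pilot duration in Section 6.2. State the calendar date or study month of the cost-effectiveness data cut.
2. List which model inputs are observed in the pilot (uptake, examinations, resource use) and which are assumed.
3. If an early model is kept, label it provisional and treat uptake as an assumption varied over a stated range.
4. Specify one re-run using attendance and resource use observed in the planned follow-up. In that run, compute uptake as examinations attended divided by examinations due, and state the convention for when an examination becomes due, including whether the entry mammogram starts the interval. The choice of convention is for the investigators.

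The cost is protocol wording and one repeat of the model, with no new data collection. The drawback is that the definitive ICER comes later than the short pilot stage.

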#### Methodology of the cost-effectiveness study

Whereas the whole pilot study aims to develop models for the personalized medicine interventions, it is not possible to predict which efficacy and effectiveness measures will be best suited to estimate the health outcomes of the program.

The planned personalized medicine interventions are preventive, and the pilot project will last less than 2.5 years, thus the most robust health outcome of mortality cannot be achieved during the study. Therefore, additional health outcomes, e.g. disease-free time to diagnosis and/or hospital care, stage of cancer diagnosed will be used to estimate the effect of preventive measures to increase the disease-free life years, postpone the negative health events, and decrease the need to use health care resources will be collected. This data will be used to model the number of events occurring in specified cohorts of persons at risk – a cohort receiving personalized preventive interventions will be compared to that on standard care.

To estimate the long-term effectiveness and costs of the new interventions, economic modeling will be used. The Markov cohort models of the natural history of BC will be constructed to assess the cost-effectiveness of preventive interventions.

The recently published cost-effectiveness studies modelling BC will be used to construct the natural history of the disease. Annual age-specific probabilities of dying from this disease and the health-related quality of life decrement during the illness will be calculated for the Swedish, Estonian and Portuguese cohorts using published cost-effectiveness studies.

The analysis results will be presented as incremental costs and quality-adjusted life-years (QALYs) gained with each intervention compared to no personalized medicine and as incremental cost-effectiveness ratios (ICERs). Both costs and utilities will be discounted at an annual rate of 5%. The sensitivity analysis will be performed by varying one or more similar parameter(s) at a time while holding other parameters at their base case value.

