### **3.3. The need for personalized risk-based screening**

Current BC screening guidelines are primarily based on age and do not support regular screening of women below the age of 50. This largely excludes young women at high risk for developing BC. On the other side, mammography screening has also potential harms and costs, therefore it is not reasonable to implement screening for all women under the age of 50. It is no longer appropriate to apply a single recommendation to women across all age groups and risk profiles and a far more precise and personalized risk estimation is needed. Screening with mammography reduces BC mortality risk 20-40% (3-5). The decline varies across age groups, ranging from 8% in the age group 39-49 years to 33% in the age group 60-69 years. The largest decrease in mortality has been shown in the age group 50-69 years, the evidence base for efficacy is weaker in younger women. The relationship between benefits and potential harms for screening in the age group 40-50 years has been controversial and in most countries

screening is not offered in this risk group. Reduced BC deaths may come at the expense of overdiagnosis (the identification and unnecessary treatment of clinically insignificant tumors), as well as the consequences of false-positive or false-negative results (5, 8).

An age-based population-level breast screening strategy that reduces BC mortality but does not account for the wide variation in individual women's cancer risks. A woman's risk of developing BC is influenced by many factors, but BC screening recommendations are based primarily on age. There are disagreements in the medical community about the optimal age to begin BC screening, as well as the frequency of screening and the age at which to stop. In Norway and mostly globally, the current BC screening guidelines do not support regular screening of women at younger ages than 50 years, thereby largely excluding potentially high-risk women from screening in younger age groups. The relationship between the benefits and potential harms of screening in the age group under 50 years has been controversial and screening is not recommended for all women under age 50. The application of personalized risks is necessary to identify those women who could benefit from the earlier start of the screening. Also, for high-risk women over age 50 current screening with 2 intervals is not optimal and may miss interval cases.

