#### **4. OBJECTIVES AND OUTCOME MEASURES**

The general aim is to perform a clinical cohort study that would test issues regarding the deployment of PRS test AnteBC and MPV-based risk testing in the Norwegian clinical setting. This clinical pilot would simultaneously evaluate logistical and ethical considerations (patient risks, feedback, operational procedures), test the flow of information, and would also create prospective performance data for PRS testing. In addition, the project will explore the relationship between PRS and mammographic density (MD).

The target group is healthy women at age 40-49, which is the age group before the current official screening. For genetic risk prediction, the project uses PRS and, if indicated, MPV tests as healthcare services with the following diagnostic screening and prevention activities.

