## **5. STUDY DESIGN**

General population-based cohort study combined with modelling studies.

The target number of study participants: 80.

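### The cost-effectiveness model takes its prevention effect from pilot outcomes in 80 women, where fewer than one cancer is expected in 2.5 years and one named measure worsens when early detection works

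*Protocol*

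**What the plan says.** Protocol section 5 describes one cohort combined with modelling: "The target number of study participants: 80". Under Methodology of the cost-effectiveness study (section 6.2), mortality is ruled out because "the pilot project will last less than 2.5 years". Other outcomes take its place: "disease-free time to diagnosis and/or hospital care, stage of cancer diagnosed will be used to estimate the effect of preventive measures". The same sentence describes success as more disease-free life years, later adverse events and less use of care. The data then feed a model that sets a personalised-prevention cohort against one on standard care.

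Section 6.2 also places the cost-effectiveness analysis in the final six months of the pilot. Section 5.2, Step 4 says "The women will be followed for 10 years", section 5.6 ends data collection after 10 years, and the synopsis gives a study period from November 2022 to November 2035.

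Section 4 adds that the pilot "would also create prospective performance data for PRS testing".

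**The concern.** There are three problems.

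- **Too few events.** Time to diagnosis and stage at diagnosis carry information only in women who develop cancer, and 80 women aged 40-49 with no sign of malignancy at entry will produce very few.
- **Wrong direction.** Variants 2 to 4 in section 5.2, Step 3 offer mammography earlier or more often than the national programme. That brings diagnosis forward and adds overdiagnosed cases, a harm named in section 3.3. Disease-free time to diagnosis then shortens when early detection succeeds, and a model that rewards longer disease-free time would count this as a loss. Enrolling more women would not cure it.
- **No fixed clock.** The period over which these outcomes are counted is not settled.

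At stake is the effect input to the incremental cost-effectiveness ratio. Cost-effectiveness is a named secondary outcome and part of a key hypothesis (section 3.7).

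**Working it through.** The protocol states no expected number of cancers, so there is no figure to reproduce.

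**Inputs**
- N = 80 (section 5).
- Ten-year risk r = 2.1% for the average woman aged 50 (sections 3.2 and 5.2, Step 3). The cohort is younger, which lowers the risk. It is also referred for symptoms, which section 5.2 says may raise it. The size of either shift is not given.
- Window T = 2.5 years (the upper limit in section 6.2) or 10 years (sections 5.2 and 5.6).

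**Expected cancers** = N × r × T/10; probability of none = (1 − r)^(N × T/10), assuming a constant hazard.
- 2.5 years: 80 × 0.021 × 0.25 = 0.42; probability of none = 0.979^20 = 0.65; probability of two or more about 7%.
- 10 years: 80 × 0.021 = 1.68; probability of none = 0.979^80 = 0.18; probability of two or more about 50%.

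**Range for 2.5 years**

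| Risk used | Source | Expected cancers |
|---|---|---|
| 1.0% to 1.5% over 10 years | assumed for ages 40-49 | 0.20 to 0.30 |
| 2.1% over 10 years | sections 3.2 and 5.2 | 0.42 |
| 1.3% over 5 years at age 50 | US study cited in section 3.5 | 0.52 |
| 3% over 10 years | top of the near-population band, section 3.5 table | 0.60 |
| 4.2% over 10 years | twice 2.1% | 0.84 (0.85 with constant hazard) |

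To expect one cancer, the cohort's average risk would have to be about 1/0.42 = 2.4 times 2.1%. Because 2.5 years is an upper limit and must also cover recruitment, actual follow-up is shorter; two years at 2.1% gives 0.34.

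**What an effect estimate needs.** Assume a two-sided 5% level, 80% power and equal groups. The Schoenfeld formula 4 × (1.96 + 0.84)² / (ln HR)² then gives about 66 events for a hazard ratio of 0.5 and 380 for 0.75. Twice the risk over the full 10 years gives 80 × 0.042 = 3.4.

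**PRS performance.** With 2 cancers and 78 non-cases and an assumed area under the curve of 0.65, the Hanley-McNeil standard error is about 0.21. The 95% half-width is 1.96 × 0.21 = 0.41, so the interval covers nearly the whole useful range.

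**Clock.** Ten years of follow-up fits a study period ending in 2035; neither fits a pilot of under 2.5 years. Counted from November 2022, the last six months of the pilot end by about May 2025 on one reading and in November 2035 on the other.

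**The case against.** The strongest defence is that the protocol claims less than this suggests. Section 6.1 makes the analysis mainly descriptive. Section 6.2 concedes that real changes in incidence and mortality cannot be analysed and that the best effectiveness measures cannot yet be predicted. Natural history, death probabilities and quality-of-life decrements come from published studies. All of that stands, and it means the ratio does not rest on the 80 women alone. It does not supply a source for the screening effect, which the text assigns to pilot outcomes.

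A reader might also infer more than the documents support:

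- **That PRS performance will be estimated from cancers in the cohort.** Section 4 does not define performance, and the PRS analyses in section 6.2 are test results, risk-group distribution and association with breast density. The sentence in section 4 only needs a limit placed on it.
- **That a missing standard-care cohort leaves the ratio undefined.** The comparator can be read as a model arm, consistent with the design in section 5 and the modelling inputs in section 4.
- **That under half a cancer is expected whatever the risk.** The table shows 0.52 to 0.85 on some inputs. Fewer than one is the defensible statement.
- **That stage is recorded only for carriers of pathogenic variants.** "Information about possible detected malignancies: Date, type, stage, TNM, morphology" appears under that heading in section 5.4, but the layout of the list cannot settle whether its last block covers everyone.
- **That the model will use too large a mortality benefit.** Section 3.3 gives a reduction "ranging from 8% in the age group 39-49 years to 33% in the age group 60-69 years", and nothing proposes the overall 20-40% as a model input.
- **That the sensitivity analysis is an error.** "varying one or more similar parameter(s) at a time while holding other parameters at their base case value" is a limited approach, but the choice between it and a joint analysis is a modelling preference.

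**Conclusion.** The point holds for the effect input to the cost-effectiveness model. As written, that input comes from outcomes that will probably not occur in the pilot window (0.42 expected, about 65% chance of none). For screening, one of the two kinds of outcome named moves against benefit. The 10-year window changes the count to about 1.7 but not the conclusion. Stage at diagnosis moves in the expected direction, though it is open to length bias and overdiagnosis and suffers from the same lack of events.

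The counts assume that 2.1% at age 50 is a fair central value for this cohort and that risk accrues evenly. The direction argument needs no figure, but applies to screening only, not to chemoprevention or risk-reducing surgery in variant carriers. The conflict between time frames is a matter of text alone.

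This should be fixed. It does not threaten the primary outcome, the proportion of women at elevated risk.

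**What to change.** - **Section 6.2, Methodology of the cost-effectiveness study:** remove disease-free time to diagnosis as an effect measure for screening. State that the screening effect in the model comes from published age-specific evidence, and that the pilot supplies risk-group distribution, uptake, attendance and cost inputs. Report any cancers and their stage descriptively.
- **Sections 5.2, 5.6, 6.2 and the synopsis:** reconcile the time frames, say what period the pilot covers, and name one data cut for the cost-effectiveness analysis, separate from the 10-year report.
- **Section 4:** state that the pilot cannot estimate how well the PRS predicts cancer.
- **Optional:** clarify in section 5.4 for whom stage is recorded, and add a joint (probabilistic) sensitivity analysis.

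The cost is minor rewording and a less ambitious claim. No additional participants are needed.
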